### *Randomization (sequence generation)*

Using statistical software, a statistician will generate a blocked randomization list that will be used to allocate patients to either the intervention or the control group. Blocks of four will be used.

### *Randomization (sequence concealment)*

Following the randomization list, 50 numbered opaque sealed and equally weighted envelopes will be given to the study coordinator. Each envelope will contain either the decision making aids (experimental group) or blank pages (control group). Allocation concealment will be

ensured since the study coordinator will have to give sequentially the sealed envelope to the enrolled patient who, once alone, will have to open it. Therefore, the study coordinator will not know in which group patients belong to.

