### **Evaluation of the aids**

In order to recruit patients with mild to severe asthma in the study, medical reports of patients attending the IUCPQ Outpatient Asthma Clinic or having participated in studies at the Research

Center will be screened by the study coordinator. Patients who will meet the eligibility criteria (see *Inclusion criteria* below) will be contacted by the asthma nurse at the Outpatient Asthma Clinic prior to their meeting with her, or by the study coordinator if patients are recruited at the research center. Relevant information on the study objectives will be given by the study coordinator to eligible patients who will be interested to participate in the study. Those who will agree to participate in the study will sign an informed consent. The study will have been approved by the institutional ethics committee. Patients who will have given feedback on the aids in step 2 will not be enrolled, according to the IPDAS criteria.

The baseline visit (visit 1A) will take place at the IUCPQ Research Center and Outpatient Asthma Clinic. With the help of the study coordinator/asthma nurse, asthma control will be assessed, using the Asthma Control Scoring System (30). The study coordinator will evaluate patients' compliance with pharmacotherapy, using the Compliance Interview Questionnaire. In addition, the Decisional Conflict Scale (18) and the Asthma Knowledge Questionnaire (31) will be filled by patients. In order to control for covariates, if relevant, data on enrolled patients' health (age, height, weight, atopy, respiratory tract infections) and environmental factors will be gathered by the study coordinator, using the IUCPQ Asthma Consultation Form. For the same reason, enrolled patients' data on asthma knowledge at baseline will also be used. Visit 1A should last about 45 minutes.

After having filled the questionnaires, the study coordinator will give patients sealed envelopes in order to randomize them in the intervention or control group (see *Randomization (sequence concealment)* below). Consequently, patients will get, or not, the shared decision making aids, depending on the group they belong to (visit 1B). Those who will belong to the experimental group will have to pass through the steps of the aids before meeting the asthma nurse. Those belonging to the control group will skip this stage and therefore will meet the nurse directly, as in usual care. In both groups, there will be one meeting with the nurse per patient.

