### ***Blinding***

The person administering the questionnaires (study coordinator) will be blinded to the group assignment as will be the persons analysing the data (study coordinator and statistician).

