### **Bias**

Convenience sampling and loss to follow-up may induce selection bias in this pilot randomised controlled trial. In order to avoid loss to follow-up, visit 2 will be scheduled at the end of visit 1. In addition, we will phone enrolled patients in the week preceding visit 2 in order to ensure that they remember their appointment at the IUCPQ Research Center.

Self-reported questionnaires are at risk of nondifferential misclassification that may weaken the effect of the aids on health issues. Although validated questionnaires are used in this study, they remain mostly subjective, and may induce information bias.

Furthermore, adherence to treatments is a complex phenomenon which has been linked to 200 different covariates (43). In addition, social pressure and lack of resources/ self-confidence are known to worsen decisional conflict (25) but will not be assessed in this study. Asthma control is also a complex phenomenon for which every single predictor will not have been assessed. Thus, residual confounding effect is possible.

Recent knowledge translation theories suggest that the knowledge translation process is more multidirectional than linear (44). Since our knowledge translation model is linear, it could not be excluded that external factors, such as health literacy and numeracy skills, may play a role in the success or failure of our intervention.

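### Coordinator blinding rests only on the patient opening the envelope alone; later steps could reveal the arm, and the bias section does not say that unblinded self-report may favour the aids

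*Protocol*

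**What the plan says.** All of this is in the protocol.

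- **Randomization (sequence generation):** a statistician produces a blocked list. "Blocks of four will be used". No ratio is given, and nothing says that the block size is kept from the coordinator.
- **Randomization (sequence concealment):** the coordinator hands out 50 numbered, opaque, weight-matched envelopes in order. They hold either the aids or blank pages, and the patient opens the envelope alone. From this the section draws its conclusion, "Therefore, the study coordinator will not know in which group patients belong to", and gives no other ground for it.
- **Blinding:** here the declaration reads: "The person administering the questionnaires (study coordinator) will be blinded to the group assignment". The same is declared for those who analyse the data, again including the coordinator.
- **Evaluation of the aids:** the coordinator screens records, informs patients and rates compliance at baseline. Then "the study coordinator will give patients sealed envelopes in order to randomize them in the intervention or control group". After that the arms part. For one arm the text is: "Those who will belong to the experimental group will have to pass through the steps of the aids before meeting the asthma nurse". The other arm takes a different path: "Those belonging to the control group will skip this stage and therefore will meet the nurse directly, as in usual care". At the two-month visit the coordinator helps patients with the same questionnaires.
- **Bias:** "Self-reported questionnaires are at risk of nondifferential misclassification that may weaken the effect of the aids on health issues". The next sentence adds that the instruments are mostly subjective and that information bias is possible, without a direction.
- **Annexe 1, Table 1:** decisional conflict, both forms of compliance and the clinical parameter of asthma control are classed as subjective and self-reported. The physiological parameter (FEV1) is classed as objective. Asthma knowledge is not in that table; its own section describes 37 items scored as right, wrong or don't know.

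**The concern.** Opening the envelope in private conceals the allocation when it is handed over. It does not keep the coordinator blind afterwards, so the conclusion in the concealment section does not follow from its premise. The Blinding section then relies on that conclusion for two later roles, outcome assessment and analysis.

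Three things are at stake. A coordinator who learns assignments and knows the block size could anticipate the next one while still screening and enrolling. A coordinator who knows the arm at two months could influence the compliance interview and the help given with other questionnaires. And a reader of the Bias section is given one direction for self-report error, towards no effect, although patients who know they received the aids may err the other way. Direction matters because the Research Utility section links possible adoption in the Quebec health system to a significantly positive effect.

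**Working it through.** **Step 1. What protects the coordinator's blinding at each stage**

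| Stage | What the protocol provides | Could the arm become known? |
|---|---|---|
| Baseline questionnaires | Completed before the envelope is given | No |
| Envelope hand-over | Opaque, sealed, equal weight, in sequence, opened alone | No |
| Between envelope and nurse | Aids first in one arm, nurse directly in the other; no equal waiting time | Yes, if the coordinator sees when the patient moves on |
| Two-month visit | Same coordinator; no instruction to patients about disclosure | Yes, if the patient says |

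The safeguards end where the arms begin to differ.

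**Step 2. Predictability from blocks of four**

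Inputs: block size 4 and 50 envelopes (protocol). Assumptions: two of each arm per block; for the worst case, the block size, block boundaries and all earlier assignments in the block are known. There are 6 equally likely orders.

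- Position 1: no information. Certain 0; best guess right 1/2.
- Position 2: the opposite arm has 2 of the 3 remaining places. Certain 0; best guess right 2/3.
- Position 3: the first two match in 2 of 6 orders, which fixes the third; otherwise it is even. Certain 1/3; best guess right 1/3 × 1 + 2/3 × 1/2 = 2/3.
- Position 4: always fixed. Certain 1; best guess right 1.

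Share certain = (0 + 0 + 1/3 + 1)/4 = 33.3%. Best-guess accuracy = (1/2 + 2/3 + 2/3 + 1)/4 = 70.8%.

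For 50 envelopes (12 full blocks plus 2):

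- Certain: 12 × 4/3 + 0 = 16 expected.
- Correct guesses: 12 × 2.833 + 1.167 = 35.2 expected, or 70.3%.

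If past assignments stay hidden, accuracy is 50% at every position. For comparison, fixed blocks of six under the same worst case give 25% certain and 68.3% accuracy, so a larger fixed block alone gains little.

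**Step 3. What differential self-report could do**

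The protocol gives no size for reporting bias, so this is illustration only. Suppose no true effect, 25 per arm, two-sided alpha 0.05, and a bias b in baseline SD units favouring the aids. With two time points and complete data, the group-by-time term is the difference in mean change. The SD of change is √(2(1 − ρ)), and its standard error is √(2(1 − ρ)) × √(2/25).

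With ρ = 0.5 the SD of change is 1 and the standard error is 0.283.

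- b = 0.2: shift 0.2/0.283 = 0.707. Rejection = Φ(0.707 − 1.96) + Φ(−0.707 − 1.96) = 0.1051 + 0.0038 = 0.109, or 10.9%.
- b = 0.3: shift 1.061. Rejection = 0.1842 + 0.0013 = 0.1855, about 18.6%.

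Over ρ from 0 to 0.7 the ranges are 7.9% to 15.0% (b = 0.2) and 11.7% to 27.8% (b = 0.3), against a nominal 5%. Nearly all of these rejections favour the aids. The values 0.2 and 0.3 borrow the effect sizes that the protocol says the Decisional Conflict Scale can detect; they are not estimates of bias.

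**The case against.** The protocol can be defended on several points, and most of them stand.

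- **The envelope procedure is sound for what it covers.** Nothing says that the coordinator waits with the patient, escorts them or sees them leave, and no duration is given for working through the aids. A reader might infer that the coordinator will know the arm; the text supports only that the coordinator could.
- **The 71% is a ceiling.** It needs every earlier assignment in the block, the block size and its boundaries. A reader might take it as the expected accuracy; the documents do not support that, and the floor is 50%.
- **The Bias section is not silent on wider bias.** It mentions information bias in general terms. A reader might infer that it presents a positive result as conservative, but no passage does so. The fair criticism is that it does not link this bias to patients knowing their arm or say that it may favour the aids.
- **Not every outcome is equally exposed.** Asthma knowledge, one of two primary outcomes, is scored on right and wrong answers, so FEV1 is not the only measure that resists reporting bias. Both primary questionnaires are completed by patients. Interviewer influence bears mainly on compliance, a secondary outcome, and on help with the asthma control score.
- **Patients cannot realistically be blinded to this intervention.** That is a limitation to state, not an error of design.

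None of this supplies what is missing: a safeguard after the envelope is opened.

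**Conclusion.** The point holds in bounded form. The protocol asserts coordinator blinding as a fact, for assessment and for analysis, on the strength of a step that secures only concealment at hand-over. Different patient flow and possible disclosure at the two-month visit could break it. How often they would is unknown.

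Predictability lies between 50% and 71%, with up to 33% of allocations certain, on the assumption of 2:2 blocks and depending on what the coordinator learns. The differential-error concern applies to decisional conflict (primary), self-reported compliance and the clinical part of the asthma control score. It is weaker for the knowledge score and for FEV1. The false-positive figures rest wholly on assumed bias and correlation and show scale only.

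This should be corrected. It does not show that the trial's allocation is compromised or that a positive result would be false.

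**What to change.** 1. **Allocation list:** regenerate it with randomly varying block sizes, for example 4 and 6, and do not disclose them to the coordinator.
2. **Visit procedure:** give every patient the same fixed time alone with the envelope before the nurse meeting. Instruct patients not to tell the coordinator their arm, including at the two-month visit. The second instruction is needed because neither varying blocks nor equal waiting deals with disclosure when outcomes are collected.
3. **Wording:** in the concealment and Blinding sections, state that patients are unblinded and that coordinator blinding is intended but may be broken. In the Bias section, state that self-report error may be differential and may favour the aids.
4. **Reporting:** show the FEV1 component of the asthma control score separately beside the global score. It is already collected.

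The cost is a new list, some text and a short wait for control patients. No extra staff are needed.

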### ***Blinding***

The person administering the questionnaires (study coordinator) will be blinded to the group assignment as will be the persons analysing the data (study coordinator and statistician).

### ***Study intervention***

In this study, the intervention is the use of shared decision making aids, which will be compared to usual care (not using the aids).

### ***Shared decision making aids***

The shared decision making aids that will be used in the intervention group will be the latest version of those developed in the previous stage of this study (developing shared decision making aids). Patients in the experimental group will receive the aids and will be asked to go through them prior to their meeting with the asthma education nurse at the IUCPQ Outpatient Asthma Clinic. During this meeting, the asthma nurse will review patient's written action plan. Individualized education and counselling will also be provided. The length of the meeting will be evaluated.

### ***Usual care***

In the control group, decision aids will not be used. As in usual care, patients meet directly the asthma nurse, who will review their written action plan, and provide individualized education and counselling. The length of the meeting will be evaluated.

### ***Operational Definitions of Dependent Variables & Measurements***

In this study, the dependent variables, or health outcomes, are asthma knowledge, decisional conflict, compliance with recommended use of pharmacotherapy, and asthma control. Covariates are asthma knowledge, age, body mass index, atopy, environmental triggers, and respiratory tract infections.

### ***Asthma knowledge questionnaire (primary outcome)***

Knowledge of asthma will be assessed by the Asthma Knowledge Questionnaire (31). The questionnaire will be filled by patients at baseline and after a 2-month follow-up. The French questionnaire comprises 37 items (true, false, don't know answers), evaluating 4 domains of asthma knowledge: biomedical, asthma severity, general knowledge and treatment (31). Developed in France, the original questionnaire had 38 items, but the eleventh has been withdrawn because it was not relevant in Quebec. The total knowledge score equals the good answers (rated 1) minus the wrong answers (rated -1). Don't know answers are rated 0. For each item, a negative score is indicative of asthma misunderstanding, a null score of a knowledge gap, and a positive score of gained asthma knowledge. The total knowledge score ranges from -37 to 37; thus, asthma knowledge will be modeled as a continuous variable. Psychometric properties of the questionnaire have been tested and showed good reliability and reproducibility (31).

### *Decisional conflict (primary outcome)*

Decisional conflict will be assessed through a French version of OHRI Decisional Conflict Scale (18). The questionnaire will be filled at baseline and after a 2-month follow-up. Sixteen items evaluate 5 dimensions of decisional conflict (informed, values clarity, support, uncertainty, effective decision) using a Likert scale. Patients' responses range from 0 (strongly agree) to 4 (strongly disagree). Patients' responses are summed, divided by 16, and multiplied by 25. Consequently, the decisional conflict score ranges from 0 (low decisional conflict) to 100 (high decisional conflict). A score greater than 37.5 suggests that there is a meaningful decisional conflict, but a score that is less than 25 is not associated with it (33). The variable will nevertheless be analysed as a continuous one. The reliability of the OHRI Decisional Conflict Scale (English low literacy version) has been evaluated using a Cronbach's  $\alpha$ , which value was above the 0.7 threshold (34). Test-retest coefficient also supports its reliability (35). The scale has been shown responsive to change, because it is able to detect an effect size of 0.2 to 0.3 in studies that compare an intervention group to a control group (33).

### *Compliance with treatments (secondary outcome)*

Compliance with pharmacotherapy in the last week will be evaluated. An interview questionnaire based on the 2003 Asthma Consensus Conference guidelines (36) and adapted to the 2012 Asthma Consensus Conference guidelines (3) will be administered at baseline and after a 2-month follow-up. It has already been used to describe the appropriate use of asthma drugs among patients with moderate to severe asthma (19). The questionnaire is composed of a set of 11 hierarchical criteria; there were originally 12, but one of them is not relevant anymore. The set of criteria evaluates, in the last week, the use and the frequency of use of controller/rescue medication, and add-on therapy (if relevant). In order to be classified as compliant, patients need to meet all the 11 criteria (19), which set patients who are very compliant apart from others (37).

The questionnaire also allows compliance to maintenance/rescue/add-on medication to be expressed as a percent score ( $[\text{doses taken}/\text{doses prescribed}] \times 100$ ). In that case, a score that is  $\geq 80\%$  but  $\leq 100\%$  is indicative of compliance (38). The variable will nevertheless be analysed as a continuous one.

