### Improving asthma control

Based on research information and effectiveness of treatment studies, Canadian Guidelines have suggested an optimal asthma management plan, which has been shown, when applied, to improve asthma control (1;7). However, many patients with asthma do not adhere to medical recommendations (4).

Adherence to treatments has first been defined as “the extent to which a person’s behaviour coincides with medical or health advice” (8). In addition, there are three components of adherence: acceptance, compliance and persistence (9). Compliance is “the extent to which a patient acts in accordance with prescribed interval and dose of a dosing regimen” (10) in order to optimize medication intake.

In asthma, both the insufficient use of controller medication and the overuse of rescue medication lead to uncontrolled asthma (11). Poor adherence with anti-inflammatory medication has indeed been shown in observational studies (12-14).

Poor adherence follows different patterns (15). Non-adherence may be unintentional, since patients may simply misunderstand their medication regimen. On the other hand, non-adherence may also be intentional, when patients worry about their medication intake and thereby decide not to fill their prescription or discontinue their treatment. In that case, poor compliance with asthma management plan is associated, among other factors, with patients' fears, misconceptions, and misunderstanding about treatments (4;16). In fact, communications are often suboptimal between patients and caregivers, who too often discuss neither patients' concerns about prescribed medication nor the pros and cons of the various recommendations (4). As a result of this, patients have to cope with a decisional conflict, which is defined as "the uncertainty about which course of action to take when choice among competing actions involves risk, loss, regret or challenge to personal life values" (17).

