### *Data analysis*

Descriptive analyses will be performed in order to describe the study population: continuous variables will be described as means or medians, depending on normality of distributions, and categorical variables as proportions.

Generalised linear models will be used to compare the intervention and control groups on the dependent variables (41). For asthma knowledge, decisional conflict, compliance with maintenance/rescue/add-on pharmacotherapy, and asthma control, a normal distribution and an identity link will be used, since all 4 variables are expressed as continuous ones. Assumptions of normality, and homoscedasticity will also be checked. A log transformation could be used to correct departure from normality, if relevant. For compliance with pharmacotherapy, a binomial distribution and a log link will be used as this variable is expressed as a binary one. In models, effects for group (intervention and control), time (baseline and 2-month follow-up) and group-by-time interaction will be included. The effect of the shared decision making aids on health outcomes will then be estimated by the interaction term between the group and time. Mean differences (continuous variables) and prevalence ratios (dichotomous variable) have been

chosen as effect measures. In addition, generalized estimating equations will be used in order to take repeated measures into account.

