If covariates (asthma knowledge, age, body mass index, atopy, environmental triggers, and respiratory tract infections) are not distributed evenly between groups, we will adjust for them in analyses. Predictors of health outcomes will be incorporated into the model as confounders if they result in a >10% change in the effect measure, following a descending procedure. Exploratory subgroup analyses according to asthma severity will be conducted since pharmacotherapy and compliance with treatments are getting more complex with the severity of the disease. Statistical interaction of body mass index will also be exploratory assessed since this covariate is hypothesized to modify the effectiveness of intervention aiming at improving asthma control (42). In addition, exploratory statistical interaction of age, education and length of the patient's meeting with the asthma nurse will be evaluated since we hypothesize that the effect measure may vary according to the level of measurement of these variables. Regarding adherence to medication, sensitivity analyses will be carried out according to different cut-offs, that will range from 60 to 80% of inhaled prescribed doses.

SAS version 9.3 (SAS Institute Inc., Cary, USA) will be used to perform the statistical analyses, using PROC GENMOD. A 2-tailed *p*-value less than 0.05 will be considered indicative of statistical significance. Since the study is a pilot, power calculation will be made *a posteriori*. Alternatively, the study size is based on the number of patients that may realistically be recruited at the IUCPQ Research Center or Outpatient Asthma Clinic according to the timeframe. Nevertheless, sample size calculations will be made during the study, based on gathered data. If feasible, more patients may be enrolled in order to get sufficient statistical power.

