**IG:** Intervention group (shared decision making) **CG:** Control group (usual care) **T1:** Baseline **T2:** 2-month follow-up

\* The effect of shared decision making aids on health outcomes will be estimated with their 95% confidence interval. The effect of the aids on asthma knowledge, decisional conflict, compliance with

controller/rescue/add-on pharmacotherapy, and asthma control will be expressed as means, since these variables are continuous. On the other hand, the effect of the aids on compliance with treatments (a binary variable) will be expressed as prevalence ratios. Both types of model will adjust for covariates, if a confounding variable results in a  $\geq 10\%$  change of the effect measure.

† P-value of the interaction term.

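### The percent compliance score has a two-sided target (80% to 100%) but is analysed as a mean difference, which has no fixed favourable direction; this is clear for rescue drugs and conditional for controller and add-on drugs

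*Protocol*

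**What the plan says.** The protocol's section *Compliance with treatments (secondary outcome)* gives two versions of compliance. The first is binary: a patient is compliant when all 11 criteria are met. The second is numerical: "The questionnaire also allows compliance to maintenance/rescue/add-on medication to be expressed as a percent score". That score is doses taken divided by doses prescribed, times 100. A value from 80% up to and including 100% indicates compliance, and the next sentence adds: "The variable will nevertheless be analysed as a continuous one". No cap at 100% is stated.

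For the continuous outcomes, *Data analysis* specifies that "a normal distribution and an identity link will be used, since all 4 variables are expressed as continuous ones", with the group-by-time interaction as the effect and a mean difference as the effect measure. Table 6 in Annexe 1 gives the controller, rescue and add-on scores a row each, and its footnote confirms that the effects on "controller/rescue/add-on pharmacotherapy, and asthma control will be expressed as means, since these variables are continuous". The binary 11-criteria outcome has its own row, with a binomial distribution and log link.

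On direction, *Hypothesis* expects compliance to improve through greater use of maintenance drugs. No direction is given for the rescue or add-on score. In the background, *Improving asthma control* says that "both the insufficient use of controller medication and the overuse of rescue medication lead to uncontrolled asthma". *Achieving asthma control* makes the same point and treats both as signs of non-adherence. The section on lessening decisional conflict through decision aids describes the goal as avoiding both overuse and underuse.

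For adherence, *Data analysis* adds that "sensitivity analyses will be carried out according to different cut-offs, that will range from 60 to 80% of inhaled prescribed doses".

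**The concern.** The same step, a threshold followed by a continuous analysis, is taken for decisional conflict and asthma control. It does no harm there, because those scales run in one direction. The percent compliance score does not: by the protocol's own definition, both 50% and 130% are non-compliant. A mean difference on that scale cannot be read as better or worse compliance without knowing on which side of the range patients started.

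Two consequences follow. For rescue drugs, an aid that corrects overuse lowers the score, so a real benefit appears as a negative difference in a row labelled compliance. For controller and add-on drugs, any over-user brought back into range pulls the mean down and offsets the gain from under-users who improve. Compliance is a stated secondary objective and the link between decisional conflict and asthma control in the protocol's causal chain, so a misread row would mislead on the mechanism.

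**Working it through.** The protocol gives no effect size, standard deviation (SD) or share of over-users for this outcome, so there is no planned figure to reproduce. The values below are assumptions, chosen to show how the scale behaves.

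**Inputs from the protocol.** Score = 100 × doses taken / doses prescribed; compliant range 80% to 100%; mean difference from a normal, identity-link model; 50 patients (taken as 25 per arm); two-sided 0.05.

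**Assumed.** In the aid arm, under-users go from 60% to 90% and over-users from 140% to 100%. Controls do not change. SD of change is 40 points, with a range of 30 to 50.

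**Step 1: the mean does not identify compliance.** Two patients at 50% and 130% average (50 + 130)/2 = 90%, inside the range although neither complies. Two patients at 90% also average 90%.

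**Step 2: offsetting within one drug class.** Let p be the share of over-users.

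- Mean difference = 30(1 − p) − 40p = 30 − 70p. It is zero at p = 30/70 = 42.9%.
- Change in mean distance from 100% = 10(1 − p) − 40.
- Power ≈ Φ(|difference| / (SD × √(2/25)) − 1.96).

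| p | Mean difference | Change in distance from 100% | Power, SD 40 (SD 30 to SD 50) |
|---|---|---|---|
| 0% | +30 | −30 | 0.76 (0.94 to 0.56) |
| 10% | +23 | −31 | 0.53 (0.77 to 0.37) |
| 20% | +16 | −32 | 0.29 (0.47 to 0.20) |
| 30% | +9 | −33 | 0.12 (0.18 to 0.09) |
| 42.9% | 0 | −34.3 | no effect to detect |
| 50% | −5 | −35 | wrong sign |

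In every row, all aid patients move from outside the range to inside it. Only the mix differs.

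**Step 3: rescue drugs.** Suppose a share q goes from 150% to 100% and the rest do not change. The mean difference is −50q: −10, −20 and −30 at q = 20%, 40% and 60%. No mix of under- and over-users is needed; the sign is negative whenever overuse is corrected.

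**Step 4: does anything else in the plan repair these rows?**

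- The optional log transformation is monotone, so 140% still ranks above 100%.
- The group-by-time term inherits the scale of the score.
- The sensitivity analyses name only lower cut-offs. If the 100% limit is kept, a 140% user fails at 60%, 70% and 80%; if it is not, that user passes all three. The text does not say which.
- The 11-criteria outcome is a separate row and leaves the percent-score rows as they are.

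**The case against.** The strongest reply has five parts.

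*Direction.* A reader might infer that the protocol treats a higher score as better for all three drug classes. It does not say so. An upward direction is stated for maintenance drugs only, the classes are modelled separately, and tests are two-tailed. A negative rescue difference could be read simply as less use relative to prescription. This stands: the defect is that the rescue row has no stated direction and is labelled compliance, not that the protocol declares reduced overuse to be harm.

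*Controllers.* The abstract and background describe maintenance drugs as underused and tie overuse to relievers. With few over-users the offset is modest (+23 instead of +30 at 10%), and the sign reverses only above 42.9% under the assumed changes. This stands too. The documents do not support the inference that all three percent-score rows fail to answer the objective; the raw controller mean matches the stated hypothesis.

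*The 11-criteria outcome.* It covers use and frequency of use of controller, rescue and add-on drugs, and it is the first secondary row of Table 6. It gives real, though partial, protection to the overall compliance conclusion.

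*Sensitivity analyses.* It is tempting to read the 60% to 80% cut-offs as dropping the upper limit. The text does not say that; it is silent, and a clarification is enough.

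*Detail left to the SAP.* Capping or scoring of values above 100% could be settled there, and no SAP is at hand. But the protocol itself fixes the continuous analysis and the mean difference immediately after defining a two-sided range, so the mismatch is in its own text.

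**Conclusion.** The point holds in a limited form. The protocol defines compliance on the percent score as a range with an upper limit, then analyses the score by a measure that ignores that limit.

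- **Rescue drugs: clear.** Correcting the overuse that the protocol names as a problem lowers the score, by 10 to 30 points when 20% to 60% of patients go from 150% to 100% (assumed).
- **Controller and add-on drugs: conditional.** The loss is 70 points times the share of over-users under the assumed changes. That share is not in the documents and may be small for controllers.

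Power figures assume 25 per arm and an SD of change of 30 to 50. The add-on row will have fewer patients, since not everyone takes add-on therapy. Severity is moderate: this is one of two versions of a secondary outcome in a pilot, no primary outcome or data collection is affected, and the 11-criteria row gives partial cover.

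**What to change.** 1. For each drug class, add to Table 6 (and list in Table 1) the protocol's own in-range indicator, 80% to 100%, analysed with the binomial log-link model already planned.
2. For each class, report the proportions below 80% and above 100% separately, so that underuse and overuse stay visible.
3. Keep the raw mean for controller drugs, where it matches the hypothesis.
4. Do not interpret the raw rescue mean difference as a change in compliance. State its direction in line with the background sections that name reliever overuse as the problem.
5. State in *Data analysis* that the 100% upper limit is kept when the lower cut-off varies from 60% to 80%.

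The absolute distance from 100% served above only as a contrast. It is not proposed as an outcome, because it scores 80% (compliant) and 120% (non-compliant) alike.

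The cost is rescoring of data already collected and edits to two sections and two tables, with no new visits or patients. The downside is precision: with about 25 patients per arm, an in-range indicator is less precise than a continuous score, so its interval will be wide.
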